#### Post LTAD insertion care

After insertion, participants will undergo ascitic fluid drainage through the LTAD in hospital, with human albumin solution (HAS) cover as per their usual LVP protocol and volume. The aim will be to safely drain the ascitic fluid, minimise the risk of leakage and cellulitis post insertion, and facilitate community management of ascites. However, in high-risk patients (those with circulatory dysfunction or chronic kidney disease) total drainage volume should be limited to a maximum of six to eight litres.

Effective communication with all relevant care teams is essential after LTAD placement. Participants and caregivers will receive clear information about the LTAD, including its use, suture removal timeline (Fig. 3), and the start of community visits. Contact details for local care teams will be provided, including details on how to access support in and out-of-hours.

**Fig. 3 Fig3:**
[figure not shown]
LTAD in situ with suggested timeline for suture removal

#### Community LTAD management

Participants will receive an initial supply of compatible drainage kits and specific trial paperwork, such as drainage diaries for community nurses to record the volume and frequency of drainage. If keen and willing, caregivers will be given an opportunity to perform the drainage themselves, supported by the community nursing teams. However, the diaries should only be completed by the community nurses, who will perform risk assessments during their home visits and raise any concerns regarding the LTAD with the research team.

Frequency and volume of drainage through the LTAD in the community will be guided by the patient’s symptoms but generally should not exceed one to two litres at each visit and no more than two to three times a week (i.e. five litres per week). This was initially based on volumes used in malignant ascites [22], but was also sufficient for ascites management in 90% of patients in the earlier feasibility study [29]. In the minority needing drainage of larger volumes, an LVP via the LTAD can be arranged in hospital, including HAS administration. Subsequent drainage volumes can then be increased in the community on a case-by-case basis.

LTAD removal should only be considered at the participant’s request, or in the event of certain complications, for example intractable infection. Continued trial participation will be encouraged, despite LTAD removal. Re-insertion of LTADs can be organised if necessary, on a case-by-case basis. Appendix 3 summarises potential complications associated with the LTAD and a recommended management protocol for each.

### Group 2 (LVP)

The control arm, intermittent LVP, is the current accepted SOC for managing patients with RA [19], typically performed in a dedicated medical day unit. Depending on site policy, patients require referral from an HCP or could self-refer for the procedure. The patient’s baseline visit will be scheduled to take place within 10 days of screening to coincide with an LVP visit in hospital.

The frequency of LVPs will depend on clinical need. Trained HCPs are expected to perform LVPs following national and local guidelines, as previously described [19]. Routine measurement of haemostatic function is not recommended [19].

### Study follow-up (both groups)

A letter confirming research participation in the trial and group allocation will be sent to each patient’s general practitioner (GP).

### Antibiotic prophylaxis

Participants in both groups will receive antibiotic prophylaxis for the duration of the study to reduce infection risk and hospitalisation. The choice of antibiotic will be left to the attending healthcare team and depend on participant’s risk profile as well as local microbiology guidance.

### Referral to palliative care

All participants will be referred to community palliative care services as standard, without a requirement for current or immediate specialist palliative care needs.

### Fortnightly home research visits

Both groups will receive home visits at fortnightly intervals (± 3 days) conducted by GCP trained staff for safety monitoring and data collection (Table 1). Visits are planned in the community but can be carried out in hospital if these coincide with an admission or a planned LVP. During the visits the drainage diaries of LTAD patients will be collected. The visits will also provide researchers with an opportunity to ensure protocol adherence, as well as to troubleshoot and report any adverse events (AEs). Routine clinical bloods will be collected unless the patient declines or is too unwell, where it may be deemed inappropriate. No specific interventions would be prohibited as part of the protocol.

### Primary endpoint/outcome

The primary outcome is the difference in the overall mean of the disease-specific HRQoL scores between both groups assessed at 12 weeks using the Short Form Liver Disease Quality of Life (SFLDQoL) questionnaire [37].

### Secondary endpoints/outcomes

Cumulative peritonitis incidenceSymptoms assessed using the Ascites-Questionnaire (Ascites-Q)[38]Informal caregiver impact assessed using the Caregiver Roles and Responsibilities Scale (CRRS)[39]Health resource utilisation using the modified Ambulatory and Home Care Record (AHCR)[40] for community service use and patient record for hospital service useGeneric HRQoL assessed using the 36-item Short Form Survey (SF-36) embedded in the SFLDQoL[37] and the EQ-5D-5L[41]Cost-utility analysis based on QALYs using EQ-5D-5LPatient, caregiver and HCP perceptions/perspectives of LTAD and LVP using qualitative methodsAssessing predictors of mortality and infection using blood and genetic biomarkers

### Questionnaire-based assessments

These will be administered as per schedule of events (Table 1) during the fortnightly home research visits. This is largely consistent with our earlier feasibility study [29].

### Liver-specific HRQoL

This will be assessed at baseline and every four weeks using the SFLDQoL [37]. The SFLDQoL questionnaire is the only validated patient-reported outcome for ACLD and predicts mortality with accuracy comparable to MELD scores [9]. It includes 36 liver specific items across nine domains (distress, stigma, memory, symptoms and effects of liver disease, sleep, hopelessness, loneliness, and sexual function) scored on a 0–100 scale, where higher scores indicate better HRQoL. Due to low completion rates in the feasibility trial [29], sexual function data will be excluded from analysis but still recorded, should participants wish to answer. The questionnaire will be completed on paper or read out by researchers for patients who are too unwell. It takes 15–20 min to complete. The questionnaire also incorporates the 36-item Short Form Survey (SF-36) [42], which assesses generic HRQoL across eight domains, forming the two physical and mental component scores (PCS and MCS). The primary outcome only includes the liver-specific HRQoL measures and the PCS and MCS will be analysed separately. Caregivers or researchers can provide proxy scores when completing the questionnaire, if necessary. Although the primary outcome focuses on the SFLDQoL scores at three months, the questionnaire will be administered every four weeks to reduce the impact of missing data and improve the robustness of the statistical analysis model.

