### Randomisation

Once an ascitic tap has excluded peritonitis (defined as ascitic white cell count > 500 cells/mm^3^ or a neutrophil count > 250 cells/mm^3^ or a positive ascitic-fluid culture result)[19] participants will be registered by the local teams on an electronic data capture platform (Ennov:MACRO™) [32] and then randomised to receive either LTAD or standard of care (LVP) in a 1:1 ratio using Sealed Envelope™ [33]. The computer-generated software will confirm the patient’s treatment group allocation. The allocation will be minimised (i.e. dynamically generated) on sex and Child–Pugh Score (CPS) with an 80% probability of assigning participants to the group that balances these factors out. This will ensure comparability of the two groups. Only the trial manager, Chief Investigator (CI), and central research team will be aware of the exact sequence of the most recent allocations. Blinding researchers or participants is not feasible due to the nature of the intervention. However, the senior trial statistician will remain blinded until final data analysis, with adverse events (AEs) coded to prevent unintentional unblinding.

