### Sample size calculation

The minimal clinically important difference (MCID) is the mean change in HRQoL scores for patients reporting a minimal yet perceptible change in health between the baseline and follow-up assessments [47]. In the ongoing LiverPal Study (one of the largest palliative trial in the USA [48], an MCID of 9 points on the FACT-Hep questionnaire was used [49]; and in a study assessing LTADs in cirrhosis,[50] an MCID of 10 points was chosen (SF-36 questionnaire[42]). While these studies show the use of MCID to inform sample size in palliative trials, neither of the tools selected are validated in ACLD. As we will be using the SFLDQoL [37], a sensitive and validated ACLD questionnaire, and to ensure a robust sample size, we have selected a MCID of 8 points.

In the earlier REDUCe trial [29], the pooled baseline mean across SFLDQoL domains (excluding sexual function) was 56.4 (SD = 26.1). With 93 participants in each group for the analysis, we will have 90% power for 5% significance to detect an adjusted difference in mean SFLDQoL scores of 8 points between the LTAD and LVP groups at the end of 3 months (effect size 0.31). This effect size falls within Cohen’s recommended cut offs for small (0.20) to moderate (0.50) effect size [51]. We assume a correlation between baseline and the 3 follow-up measurements of 0.48 which is the lower bound of the 95% confidence interval for the correlation from the feasibility data (point estimate 0.77) [29]. With an expected 40% attrition [29], we will recruit 310 participants in total for the trial. The sample size was calculated using Stata (version 17.0).

Following on from lessons learnt during the earlier feasibility study [29], to improve study retention, the protocol allows for proxy-scores to be collected on behalf of patients who may be too unwell to complete the questionnaires themselves. Secondly, appointment of consultees who can be approached in case of loss of capacity during the trial follow-up period will allow patients to be retained even in case of disease progression. Finally, to prevent recruitment late in their disease trajectory, we are providing communication skills training for researchers to facilitate difficult palliative care discussions.

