**Fig. 4 Fig4:**
[figure not shown]
CONSORT diagram. Abbreviations: n number, LTAD long-term abdominal drain, LVP large volume paracentesis

For the primary outcome, the analysis will follow intention-to-treat principles and will be conducted using a linear mixed effects model. All patients randomised through Sealed Envelope will be included in the group to which they were allocated regardless of the outcome or clinical trajectory.

This model will include fixed effects: time point, sex, Child Pugh score, randomisation group, and an interaction between randomisation group and time point, while adjusting for baseline SFLDQoL scores. A random effect for participant will be included to handle the correlation between repeated measurements across the study period. The model parameters will be estimated using restricted maximum likelihood, and treatment differences between groups at each follow-up will be reported along with 95% confidence intervals and p-values. Secondary outcomes will similarly be analysed using mixed effects regression models suited to the type of outcome.

Subgroup analyses will aim to stratify data based on patient and site-level characteristics. Patient-level factors will include liver prognostic scores baseline ascitic fluid protein level, socioeconomic status, and the presence of informal caregivers. Site-level data will include prior experience with LTADs, availability of dedicated LVP units, cirrhosis nurses, Palliative care MDTs for ACLD, and Improving Quality in Liver Services (IQILS) programme accreditation. Subgroup analyses will allow for the identification of potential effect modifiers or predictors of outcomes and changes in HRQoL.

Only in the case of significant protocol deviations, agreed with the CI, will participants be excluded from the final analysis. In accordance with MORECare guidance for palliative trials, attrition due to mortality, illness, and withdrawal will be detailed for each group [53]. Missing quantitative data will be assumed to be missing not at random (MNAR) unless evidence suggests otherwise. Imputation models will be utilised followed by sensitivity analyses using plausible adjustments to explore the potential impact of missing data and MNAR assumptions on treatment outcomes (multiple imputation with delta adjustment).

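### Unblinded researchers may supply proxy scores on the primary quality-of-life outcome, and the analysis described in the article does not separate these from self-report

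*Protocol article*

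**What the plan says.** The primary outcome is the between-group difference in mean score, "assessed at 12 weeks using the Short Form Liver Disease Quality of Life (SFLDQoL) questionnaire" (Primary endpoint/outcome). The article describes the instrument as patient-reported: "The SFLDQoL questionnaire is the only validated patient-reported outcome for ACLD" (Liver-specific HRQoL).

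That section gives two kinds of help. The first is assistance with completion: "The questionnaire will be completed on paper or read out by researchers for patients who are too unwell". The second goes further: "Caregivers or researchers can provide proxy scores when completing the questionnaire, if necessary". The sample size section gives the purpose. To improve retention, "the protocol allows for proxy-scores to be collected on behalf of patients who may be too unwell to complete the questionnaires themselves".

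On blinding, the Randomisation section says "Blinding researchers or participants is not feasible due to the nature of the intervention". The only role named as blinded is the statistician: "the senior trial statistician will remain blinded until final data analysis".

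On analysis (Statistical analysis, text after Fig. 4), "This model will include fixed effects: time point, sex, Child Pugh score, randomisation group, and an interaction between randomisation group and time point", with adjustment for the baseline score and a random effect for participant. The sensitivity analyses named there concern missing data: multiple imputation with delta adjustment.

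**The concern.** The sentence on proxy scores lets a member of the research team, who knows the allocation, put a number on the primary endpoint in place of the patient. Several of the listed domains (distress, stigma, hopelessness, loneliness) are largely internal states that another person sees only in part. Others, such as symptoms and sleep, are easier to observe. Questionnaires are given at the fortnightly visits, where staff also collect the drain diaries of the LTAD group, so the allocation is in plain view when a rating is made.

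If raters lean differently in the two arms, the difference goes directly into the treatment effect. The planned delta adjustment would not touch it, because a proxy score counts as an observed value. The article recognises the general risk under Harms and safety monitoring, where adverse events are compared regardless of judged relatedness because the trial is open-label. It describes no counterpart for the primary outcome.

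**Working it through.** **1. Is proxy scoring different from reading aloud?** Yes. The two are separate sentences in Liver-specific HRQoL. The sample size section describes proxy scores as given on behalf of patients too unwell to complete the form.

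**2. Are the raters unblinded?** Yes, by the Randomisation section. Caregivers also know the arm.

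**3. Do proxy scores enter the primary analysis alongside self-report?** This is inferred, not stated. They are collected to improve retention, so they are meant to be used. The listed model terms are time, sex, Child Pugh score, group, group × time, baseline and participant, with none for respondent type. The sensitivity analyses described address missing data only.

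**4. The plan's own precision.** Inputs from the sample size section: difference 8, SD 26.1, correlation 0.48, three follow-ups, 90% power, 5% significance (taken as two-sided), 93 per group, 40% attrition.

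- Variance factor for baseline-adjusted repeated measures: (1 + 2 × 0.48)/3 − 0.48² = 0.6533 − 0.2304 = 0.4229.
- n per group = 2 × (1.960 + 1.282)² × 26.1² × 0.4229 / 8² = 94.6, so 95. With the rounded effect size 0.31: 2 × (1.960 + 1.282)² × 0.4229 / 0.31² = 92.5, so 93, as stated.
- 93 / (1 − 0.40) = 155 per group, 310 in total, as stated.
- Standard error of the difference: 26.1 × √0.4229 × √(2/93) = 2.49.

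The sample size reproduces, and the point does not depend on it. It only supplies the scale for the next step.

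**5. Size of the bias.** Let q be the share of scores given by proxy (taken as equal in the arms) and b the between-arm difference in mean proxy error. The shift in the treatment difference is about q × b. The documents give neither, so both are assumptions.

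| q | b (points) | Shift q × b | Share of 8 points | Two-sided type I error, SE 2.49 |
|---|---|---|---|---|
| 10% | 5 | 0.5 | 6% | 5.5% |
| 20% | 10 | 2.0 | 25% | 12.7% |

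Type I error is 1 − Φ(1.96 − shift/SE) + Φ(−1.96 − shift/SE). The SE of 2.49 averages over three follow-ups. If the 12-week contrast stood alone, the factor would be 1 − 0.48² = 0.7696, the SE 26.1 × √0.7696 × √(2/93) = 3.36, and the two error rates about 5.3% and 9.2%.

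Here q covers all proxies. Barring researchers alone would remove only the researcher part, which cannot be estimated from the article.

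**6. Price of setting proxy scores aside.** If proxy-scored participants were lost altogether from the 93 per group, power would fall from about 90% to 86% at q = 10% (83.7 per group) and 82% at q = 20% (74.4 per group). This is pessimistic, since their earlier self-reports would still contribute.

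**The case against.** The strongest reply is that proxy scoring is a deliberate trade-off. The article draws it as a lesson from the feasibility trial, expects 40% attrition, and assumes that data are missing not at random. Without a proxy, the score of a very sick patient is often missing, and that carries its own bias. Patients without a caregiver are eligible (Characteristics of participants), so for some of them a researcher may be the only proxy. This stands as a real cost. It does not settle the matter, because the article has a stated method for missing scores and describes none for rater error.

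Second, knowledge of the arm and limited view of internal states apply to caregivers as well. That also stands, and it is why a check is needed on all proxy scores, not only on those from researchers.

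Third, patients are unblinded too, so self-report already carries expectation effects. Proxy rating adds a route to an existing risk and is not its only source.

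Fourth, a reader might infer that the trial pools proxy and self-report as a matter of plan and that no planned analysis could reveal the effect. The documents do not support that. The article is condensed and never says how proxy scores are treated, and the full protocol and any SAP may record respondent type or analyse by it. Neither, however, would undo the permission itself, which the article states as a rule of conduct.

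A reader might also infer that the bias is known to be large, or that barring researcher proxies would cost only a few scores. The article gives no proxy share, no split between researchers and caregivers, and no timing of proxy use, so neither claim can be made.

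**Conclusion.** The point holds in a limited form. The article expressly allows unblinded researchers to rate the primary outcome for the patient, beyond reading it aloud. Proxy scores are meant to aid retention, and the analysis described does not separate them, so arm-dependent rater error could reach the primary estimate without being touched by the delta adjustment.

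The size is unknown. Under the assumed inputs it runs from minor to material, at 0.5 to 2 points against a target of 8. The upper case assumes a 10-point arm difference in proxy error, which is larger than the target itself. The change is a cheap improvement to a design choice; nothing here shows that the trial's result would be wrong.

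**What to change.** - Amend the proxy sentence under Liver-specific HRQoL so that researchers only read items aloud and record the patient's own answers, with proxy rating limited to caregivers.
- Record on every remaining form who answered: the patient alone, the patient with items read aloud, or a caregiver.
- Where past researcher-rated scores can be identified, treat them as missing in the primary analysis under the imputation already planned. Where they cannot, say so in the report.
- Add a sensitivity analysis that sets all proxy scores to missing, since caregivers also know the arm.
- Report by arm the number of proxy scores and the number of 12-week scores missing as a result of the change.

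This takes one amended sentence, one form field and one analysis. The senior statistician is blinded until final analysis and the last visit is planned for September 2026, so the rule can be set without sight of results. The downside is more missing 12-week scores, mainly in very unwell patients without a caregiver. Recruitment began in November 2022, so the step for past scores depends on what the existing forms recorded.

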### Ascites-Q

Symptom burden will be assessed at baseline and fortnightly using the Ascites-Q tool validated in patients with ascites due to cirrhosis [38]. It is an 11-item questionnaire (abdominal pain, fullness, loss of appetite, satiety, nausea, shortness of breath, back pain, mobility, fatigue, sleeping issues, size of abdomen). Each symptom is assessed based on frequency (6-point Likert scale “never” to “always”) and discomfort (5-point Likert scale “not at all” to “a lot”). A higher summative score indicates a higher symptom burden. It takes 5–10 min to complete.

### Caregiver Roles and Responsibilities Scale (CRRS)

For caregivers who consent to participate in the study, the validated Caregiver Roles and Responsibilities Scale (CRRS) questionnaire will assess their care workload [39], completed at baseline and every four weeks. The CRRS, validated in the cancer setting, evaluates the impact on caregivers of providing support, across 41 items in five subscales: Support and Impact, Lifestyle, Emotional Health and Wellbeing, Self-care, and Financial Wellbeing, plus three standalone items. For employed caregivers, an additional Jobs and Career subscale can be calculated. The total CRRS score ranges from 0 to 152, with lower scores indicating higher caregiver burden. Missing data can be prorated if the completion rate is over 50% per subscale and 80% overall. It takes 10–15 min to complete.

#### EQ-5D-5L

EQ-5D-5L will also be administered at baseline and fortnightly visits. It has five dimensions (mobility, self-care, usual activities, pain/discomfort, and anxiety/depression) rated on a 5-point Likert scale (“no problems” to “severe problems/ unable”) [41]. Responses will be converted to a health utility value to calculate QALYs. The tool also includes a 20 cm vertical Visual Analogue Scale (VAS), capturing the patient’s overall perception of their health with range 0 (worst) to 100 (best). It takes 5 min to complete.

